# List of abbreviations

AE Adverse Event

AR Adverse Reaction

ASR Annual Safety Report

BMI Body Mass Index

CF Cystic Fibrosis

CFQ-R Cystic Fibrosis Questionnaire – Revised

CI Chief Investigator

CRF Case Report Form

DMC Data Monitoring Committee

EPDS Edinburgh Postnatal Depression Score

ETI Elexacaftor-Tezacaftor-Ivacaftor

EQ-5D-5L EQ-5D-5L (this is the full name of the questionnaire)

(pp)FEV_1_ (percentage predicted) Forced expiratory volume in 1 second

FVC Forced vital capacity

GAfREC Governance Arrangements for NHS Research Ethics

GCP Good Clinical Practice

HRA Health Research Authority

HRQOL Health related quality of life

ICF Informed Consent Form

IQR Interquartile range

ISF Investigator Site File

ISRCTN International Standard Randomised Controlled Trial Network

LCI Lung Clearance Index

LTOT Long term oxygen therapy

MCID Minimally clinically important difference

MIC Minimally important change

MBW Multiple Breath Washout

NICE National Institute for Health and Care Excellence

NHS R&D National Health Service Research & Development

PI Principal Investigator

PIS Participant Information Sheet

QA Quality Assurance

QC Quality Control

RBHH Royal Brompton and Harefield Hospitals

RCT Randomised Control Trial

REC Research Ethics Committee

SAE Serious Adverse Event

SAR Serious Adverse Reaction

SD Standard deviation

SDV Source Document Verification

SOP Standard Operating Procedure

SSA Site Specific Assessment

TMG Trial Management Group

# Study synopsis

| **Full study title:** | An observational study to evaluate the impact of pregnancy and parenthood in females with Cystic Fibrosis and their offspring in the CFTR modulator era. |
| --- | --- |
| **Short study title:** | MATeRnal, InfAnt, Reproductive & Child Health in Cystic Fibrosis (MATRIARCH_CF) |
| **IRAS ID number:** | **352398** |
| **Chief Investigator:** | [name] |
| **Lead Co-ordinating Investigator** | [name] |
| **Study centres/sites:** | Royal Brompton Hospital (RBH), Guy’s and St Thomas’ Hospitals NHS Foundation Trust, [name] |
| **Study duration:** | Three years |
| **Primary Aims:** | 1. **Sub-study ‘Mama’**: To describe the impact of pregnancy and the first 12-24 months of parenthood in females with cystic fibrosis on their physical and psychological health. 2. **Sub-study ‘Mini’ & ‘Midi’:** To collect clinical data that will enable assessment of health outcomes in offspring of parents with CF in the short (up to 24 months) and medium-term (aged three-to-six years) |
| **Primary Objectives:** | 1. **Sub-study ‘Mama’**    1. To record the obstetric and neonatal outcomes of females with CF.    2. To record CF-related health outcomes among females with CF including pulmonary (e.g. ppFEV_1_) and nutritional status (e.g. BMI) during pregnancy and early parenthood (up to 24 months).    3. To record the subjective experiences of family planning, pregnancy and early parenthood in females with CF.    4. To describe the impact of diabetes (pre-existing and gestational) on obstetric, neonatal and CF related outcomes.    5. To record sweat chloride results during pregnancy and/or lactation among females with CF in relation to CFTR modulator therapy. 2. **Sub-studies ‘Mini’ and ‘Midi’**    1. To collate clinically obtained serum liver enzymes levels and to record the frequency of congenital abnormalities (including ophthalmic cataract screening), in children born to a parent with CF (females or males with CF).    2. To document cases of ‘missed’ CF-diagnoses due to false negative immunoreactive trypsinogen (IRT) results in children of females with CF in relation to transplacental and/or lactational exposure to CFTR modulators.    3. To record lung function indices using lung clearance index (LCI) of young children (aged three-to-six years) born to a parent with CF. |
| **Exploratory Objectives:** | 1. **Sub-study ‘Mama’**    1. To provide biological samples to facilitate validation of a measurable assay for the individual components of CFTR modulators in maternal blood and breastmilk.    2. To record maternal serum and urine hormonal and micro-nutrient changes through pregnancy.    3. To review lower respiratory tract microbiology in relation to pulmonary status (e.g. pulmonary exacerbation frequency and haemoptysis) among females with CF during pregnancy and early parenthood (up to 24 months).    4. To identify changes in maternal bronchial artery size during pregnancy with antenatal radiological imaging (MRI) and explore rates of haemoptysis in pregnant and post-partum females with CF.    5. To identify structural lung changes and functional impacts using oxygen-enhanced lung MRI (OEMRI) during pregnancy.    6. To document fetal radiological findings in relation to embryological ophthalmic and pulmonary development. 2. **Sub-studies ‘Mini’ and ‘Midi’**    1. To record blood pressure and cranial ultrasound measurements in children born to a parent with CF.    2. To record routine neonatal health outcomes, offspring growth and developmental milestones in children born to a parent with CF.    3. To record lung MRI results in young children (aged three-to-six years) born to a parent with CF.    4. To provide biological samples to facilitate validation of a measurable assay for the individual components of CFTRm in the blood of babies exposed to CFTRm in utero and/or via lactation. |
| **Study population:** | 1. Females aged 16 years or older with CF under the care of the Royal Brompton Hospital adult CF Unit who are planning a pregnancy or pregnant. 2. Biological offspring of people with CF (both mothers and fathers) cared for by the Royal Brompton Hospital Adult CF Service, from birth to the age of six years. |
| **Methodology:** | This is a non-commercial, observational mixed-methods study comprising three linked sub-studies named: **MATRIARCH_CF:** **‘Mama’, ‘Mini’, and ‘Midi’.**  A single, over-arching study protocol is warranted due to a continuation of participants, themes and data-sharing from pregnant subjects (‘Mama’) and subsequent in utero environment in their offspring (‘Mini’ and ‘Midi’).  As an observational study, all the assessments described below will be optional, and participants will not be excluded from the study if they wish to decline specific investigations.  ***Sub-study 1 – ‘Mama’ (pre-conception, pregnancy and parenthood)***  ‘Mama’ is a sub-study of pre-conception, pregnancy and parenthood in adult females with CF. This is a prospective, mixed-methods, observational cohort study, collecting data generated in a clinical setting through the local Royal Brompton Hospital CF Reproductive and Maternal Health Service.  ***Sub-study 2 –’Mini’ (Offspring 0 - 24 months)***  The ‘Mini’ sub-study is a prospective, observational cohort study of children who have at least one biological parent with a diagnosis of CF. It is expected that many, but not all, of these children will be those born to females participating in the ‘Mama’ sub-study.  There will be a maximum of four visits in two years, with visits including physical examination, specimen collection (blood, sweat, faeces), and imaging (cranial ultrasound).  ***Sub-study 3 –’Midi’ (Offspring 3 – 6-year-olds)***  ‘Midi’ is a cross-sectional, cohort sub-study of children aged three-to-six years who have at least one biological parent with a diagnosis of CF. Participants from ‘Mini’ will be eligible to progress into the ‘Midi’ protocol once the appropriate age has been reached.  There will be a maximum of two visits, with visits including physical examination, specimen collection (sweat), lung function testing and imaging (lung MRI). |
| **Eligibility criteria:** | ***Inclusion criteria – ‘Mama’ sub-study:***   - Written informed consent obtained from participant. - Under the care of Royal Brompton Hospital CF Reproductive and Maternal Health Service - Age 16 years or above at time of recruitment - Confirmed diagnosis of CF - Planning a pregnancy or pregnant at time of recruitment. - Ability to adhere to the required visits and investigations.   ***Inclusion criteria –’Mini’ sub-study:***   - Written informed consent obtained from participant’s legal guardian. - Infants who have a biological parent with a confirmed diagnosis of CF under the care of Royal Brompton Hospital Adult CF Service - Less than 12 months of age at first visit. - Ability to adhere to the required visits and investigations.   ***Inclusion criteria –’Midi’ sub-study:***   - Written informed consent obtained from participant’s legal guardian. - Children who have a biological parent with a confirmed diagnosis of CF who is under the care of Royal Brompton Hospital Adult CF Service. - Age three to six years at time of visit - Ability to adhere to the required visits and investigations. |
|  | ***Exclusion criteria – ‘Mama’ sub-study:***   - Any significant health condition which would cause inability to comply with protocol based on investigator discretion. - History of lung transplantation   ***Exclusion criteria – ‘Mini’ sub-study:***   - Legal guardians’ inability to provide consent to participate in the study. - Mother of infant has significant comorbidities unrelated to CF which could affect infant outcomes based on investigator discretion. - A significant comorbidity in the infant unrelated to CFTR modulator exposure which could affect their outcomes, based on investigator discretion.   ***Exclusion criteria – ‘Midi’ sub-study:***   - Legal guardians’ inability to provide consent to participate in the study. - A significant health condition which is known to affect lung function or imaging based on investigator discretion |

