### Blood test for CFTRm assay and serum save

During the same procedure as the liver function blood tests, around 200 microliters of blood will be collected for qualitative and quantitative analysis of CFTRm and their major metabolites using LC-HRMS or LC-MS/MS and storage. If there is remaining sample, it will be stored and frozen for potential future analysis of other tests if emerging research suggests this is necessary.

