## Data handling and analysis

REDCap is a secure password protected web-based database which will be used for data entry, storage and analysis. Disaster recovery of this data is included on these servers, with files regularly backed up.

The CRF saved on REDCap will be designed to ensure all the required data is collected. The sub-investigators and other delegated staff will be responsible for data entry. Staff will be trained to ensure consistency in data input and adherence to the protocol.

All samples transferred to other sites will only be coded with data ID rather than patient identifiable data. Results of this will be processed in batches and the results returned to researchers via a secure transfer.

Data analysis will be done when final study data is available as no formal interim analysis is planned, and prior to this a statistical analysis plan will be written, taking into account the numbers recruited.

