5. Number of participants with raised intracranial pressure diagnosed on cranial ultrasound (‘Mini’ only)
6. Validation of a CFTRm assay in serum (‘Mini’ only)
7. Abnormal lung branching on lung MRI. (‘Midi’ only)

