## Sample size and recruitment

### Sample size calculation

This is an observational study designed to inform potential future studies. Recruitment will be pragmatic and designed to maximise participant numbers, without a pre-determined sample size from within a limited pool.

There are currently insufficient studies to provide data for power calculations. This study will provide pilot data to help inform whether further studies are warranted and provide data to power future studies.

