### Planned recruitment rate

***‘Mama’ sub-study***

The aim of recruitment will be to maximise number of participants in the study. Approximately 15 women complete a pregnancy (give birth to a live infant) a year at the Royal Brompton Hospital CF Maternal Health Service, and patient involvement workshops indicate approximately two-thirds would be inclined to enrol in the trial. Due to the follow up duration we would expect to be able to recruit 20-25 participants.

Participants will be eligible to enrol at any stage in their pregnancy and will be consented for retrospective access to clinical data collected prior to enrolment that is included in the study.

*‘****Mini’ sub-study***

Mirroring the Mama sub-study, with most infants expected to be enrolled via this route, this will provide an overall pool of 15 babies per year. With two-thirds expected to enrol this will lead to around 10 infants per year. Children already born and under the age of 12 months at first visit can also be included which will add an estimated five further infants to the study. Overall, the expected recruitment over 3-year period will be 25 – 35 infants.

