### Primary endpoint analysis

A descriptive analysis of the endpoints will be completed. For categorical variables (e.g. presence of cataracts) they will be summarised as frequencies (%). For continuous variables (e.g. weight centiles) they will be reported as a mean (standard deviation) or median (inter-quartile ranges) dependent on sample distribution.

For comparisons across CFTRm exposed and non-exposed groups, a chi-square or Fisher’s exact test will be used for categorical variables, and a two-sample t-test or Mann-Whitney U test for continuous variables. Confounders including but not limited to cumulative time of exposure to CFTRm, maternal health, and gestation of offspring will be considered.

In the ‘Mini’ sub-study, enrolling offspring for their first visit up to the age of 12 months allows for maximising sample size although resulting in the possibility of missing early life events. A sensitivity analysis to test assumptions such as only including those up to six months of age will be undertaken.

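### Measured CFTR modulator levels are used only to validate the assay, and cumulative exposure time is called a confounder although it measures exposure

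*Protocol*

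**What the plan says.** **Measurement.** Table 1 (9.3.1) schedules a maternal blood sample for the CFTRm assay at all eight 'Mama' visits. Milk is sampled at up to three visits, if the woman breastfeeds while on CFTRm. The sweat test is at five of the same visits. Table 2 (9.4.1) schedules the assay for exposed 'Mini' infants at visits 1 and 2, and at visits 3 and 4 only with recent exposure through breastfeeding. Section 9.4.7 describes the infant sample: "During the same procedure as the liver function blood tests, around 200 microliters of blood will be collected for qualitative and quantitative analysis of CFTRm". Under 13.3, samples sent to other sites yield data for the team: "Results of this will be processed in batches and the results returned to researchers via a secure transfer".

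**Stated use.** The exploratory objective for infants is to support "validation of a measurable assay for the individual components of CFTRm in the blood of babies exposed to CFTRm". The 'Mini' endpoint in 15.2.2 is "Validation of a CFTRm assay in serum", and the 'Mama' endpoint is the same for serum and milk. No objective or endpoint links a measured level to an outcome.

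**Analysis.** Section 15.4.2 names chi-square or Fisher tests and t or Mann-Whitney tests "For comparisons across CFTRm exposed and non-exposed groups". It then lists cumulative time on CFTRm among the confounders to be considered. Section 9.4.4 records the timing and months of in-utero and of breastfeeding exposure separately.

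**Numbers.** No sample size is fixed: "There are currently insufficient studies to provide data for power calculations". For 'Mini', "Overall, the expected recruitment over 3-year period will be 25 – 35 infants".

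**The concern.** Two things are given the wrong role.

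**The levels.** Primary objective 1.5 asks for maternal sweat chloride in relation to modulator therapy, and level and sweat are sampled at five shared visits, yet no endpoint joins them. For infants, 4.2.2 cites a raised AST that settled when formula was increased relative to breast milk, and enzyme rises in infants exposed through lactation. A yes/no variable scores a formula-fed infant exposed only in utero the same as a breastfed infant with drug in the blood.

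**Exposure time.** A confounder is a separate cause of the outcome that is associated with exposure. Months on CFTRm are the amount of exposure. They are zero in every unexposed child, so adjusting for them cannot make the two groups more comparable. It splits the exposure effect between two coefficients.

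At stake is how much the study can say about liver enzymes and sweat chloride, and how useful it is as pilot data, its purpose under 15.3.1.

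**Working it through.** **1. The plan's own recruitment figure.** Section 15.3.2 gives 15 babies a year and two-thirds enrolling: "With two-thirds expected to enrol this will lead to around 10 infants per year". It adds five infants already born. Over two to three years of intake, 10 × 2 + 5 = 25 and 10 × 3 + 5 = 35. The stated 25-35 is reproduced.

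**2. Unexposed infants (assumption).** Section 4.1 says about 90% of women with CF continue CFTRm in pregnancy. If only the other 10% supply controls, that is 2.5 of 25 to 3.5 of 35, or about 2-4 infants. Infants of fathers with CF are also eligible (section 8), but their number is not given. An assumed upper share of 40% gives 10-14. The range is 2-14.

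**3. What each analysis could detect.** Two-sided 5% and 80% power are assumed, as the protocol states neither. The difference *d* (in SDs) comes from the noncentral t with noncentrality d × √(n1·n0/(n1+n0)). The correlation within exposed infants, all assayed, is |r| = tanh[(1.96 + 0.84)/√(n1 − 3)].

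| Infants | Unexposed share | Exposed v unexposed | Detectable d | Detectable r among exposed |
|---|---|---|---|---|
| 25 | 10% | 23 v 2 | 2.16 | 0.56 |
| 30 | 10% | 27 v 3 | 1.77 | 0.52 |
| 35 | 10% | 31 v 4 | 1.53 | 0.48 |
| 25 | 40% | 15 v 10 | 1.19 | 0.67 |
| 35 | 40% | 21 v 14 | 1.00 | 0.58 |

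If only 12-16 infants have a sample, the detectable |r| is 0.73-0.65.

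**4. The liver endpoint as listed.** Section 15.2.1 counts infants with an enzyme above the upper limit, so Fisher's test applies. With 27 v 3 and no control event, p ≤ 0.05 needs events in at least 19 of the 27. For an illustrative 30% v 5%, power is under 1% at 10% unexposed and about 10-28% at 40%.

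**5. Does using the level help?** This depends on the mechanism. Simulation with a continuous log ALT, 40-60% of exposed infants breastfed on CFTRm, and a level CV of 60%:

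| Assumed truth | t-test, exposed v unexposed | Regression on level, exposed only |
|---|---|---|
| 1 SD rise at the mean breastfed level (25 v 3-8) | 5-19% | 75-84% |
| 1 SD rise from in-utero exposure only | 35% (25 v 3), 50% (25 v 5), 80% (21 v 14) | about 5% |
| No drug effect, but breastfed infants differ by 0.5 SD (21-25 exposed) | not the issue | 12-16% false positives |

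The second row's t-test figures follow from the formula in step 3; for example √(25·3/28) = 1.64 gives 35%. In the third row the regression picks up feeding mode, because level is zero in every formula-fed infant.

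**The case against.** The strongest reply is that this is an omission from a descriptive pilot. A statistical analysis plan is still to be written (13.3, 15.1), nothing forbids a level analysis, and validating an assay before relying on it is sound sequencing. The objectives promise to collate and record, not to run a powered test. This stands in part: no figure is wrong and the validation endpoints should remain. But the protocol itself fixes the role of the levels and of exposure time, and an analysis plan written to those endpoints would carry both forward.

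Several stronger readings are not supported:

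- **That a level analysis is far more powerful in general.** It is so only if the effect follows the current level. If the effect is in utero, a central part of the study's rationale, the ranking reverses (step 5).
- **That exposed infants with low levels are clean internal controls.** Level is largely feeding mode, which may affect liver enzymes by itself.
- **That exposure is recorded only as yes or no.** Section 9.4.4 records months by route, and 15.4.2 mentions cumulative time.
- **That controls are certainly a handful.** Their number is not stated.
- **That every infant has a paired level and liver test.** All assessments are optional (6.1). For infants with continuing exposure, 9.4.6 records the routine liver test nearest the visit, which may not be the same draw.

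**Conclusion.** The point holds as a missed use of data and a misassigned variable. Quantitative levels are collected but their stated use ends at validation, and cumulative exposure time is named a confounder when it is an exposure measure.

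The remaining contrast is weak across the plausible range. It detects about 1.0 to 2.2 SD at 80% power, with 2-14 unexposed among 25-35 infants. By itself it does not distinguish exposure before birth from exposure through milk. This rests on the assumed unexposed share of 10-40%, two-sided 5% and 80% power.

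A level analysis would complement the contrast, not replace it. With all exposed infants assayed (about 23-31 at a 10% unexposed share) it detects only |r| of about 0.5 or more, and it needs a stronger relation with fewer infants. It cannot show in-utero effects. It does not apply to congenital outcomes or to 'Midi', which has no assay.

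**What to change.** 1. Keep the validation endpoints and the exposed v non-exposed comparison.
2. In 15.2.2, add as exploratory endpoints the measured concentrations, with milk:maternal and infant:maternal ratios.
3. In 15.4.3, add an exploratory analysis within exposed 'Mini' infants of continuous ALT and AST against the infant level, where both come from the same visit's draw. Give an estimate with a 95% CI, overall and within breastfed infants (or adjusted for the feeding history in 9.4.4).
4. For 'Mama', relate sweat chloride to the same-visit maternal level within woman, to serve objective 1.5.
5. In 15.4.2, move cumulative exposure time out of the confounders. Treat it as an exposure measure, split into in-utero and lactation months.
6. Use only components whose assay validates, and state how results below the limit of quantification are handled.

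The cost is wording and a little analysis, with no new sample or visit. The analysis depends on the assay working and on uptake of optional sampling, so it should be labelled exploratory and read through its intervals.

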# Introduction

## Background

Almost all studies on the outcomes of pregnancy in females with cystic fibrosis (CF) were limited by small sample sizes and occurred prior to the widespread availability of CFTRm. Females with CF were found to have poorer outcomes, with a higher risk of pre-term birth, gestational diabetes and congenital abnormalities (1). Updated studies are now required to review if these prior conclusions are still valid given the increased health stability and improved survival conveyed by modulator therapy. Since the widespread introduction of CFTRm, there has been an associated dramatic increase in the number of pregnancies amongst females with CF (2,3), making this study important and timely.

Consistent with most novel drug therapies, females who were pregnant or actively trying to conceive were excluded from CFTRm clinical trials, meaning that all data on these medications during pregnancy has been gathered from retrospective reviews and case studies. Without robust evidence, decisions around continuing or ceasing CFTRm prior to or during pregnancy are challenging, particularly as CFTRm remain unlicensed for use in pregnancy. Despite this approximately 90% of females with CF elect to continue CFTRm during pregnancy (4). There have been reports of health decline in females with CF who have stopped CFTRm therapy during pregnancy (5), however this must be weighed against the potential for, as yet unknown consequences to the developing fetus.

Data from animal models has shown that all components of CFTRm drugs (most commonly used: elexacaftor, ivacaftor and tezacaftor (ETI) (6)) cross the placenta and thus result in a degree of fetal exposure. Although no specific therapeutic drug monitoring is available, studies did show that ETI levels have been found to be comparable in maternal, cord and infant blood, suggesting a therapeutic concentration(7). Low levels of ETI were also found in breastmilk.

Due to the rapidly changing landscape of CF health, there are no consensus guidelines currently for what, if any, clinical follow up or investigations those children born to females with CF should have. Suggestions from limited data concentrate on ophthalmological reviews for potential cataracts, and regular liver function testing in infants with continued drug exposure via breast feeding (7), but these are yet to become standardised or adopted into common practice.

An additional concern is the reported cases of infants with CF who had a delayed diagnosis due to a false negative newborn screen (9). This has occurred as a result of sufficient in utero absorption of ETI as to result in a negative screening result, due to correction of their CFTR function. These cases are rare but have serious health implications for the child who would have a delay in appropriate care and intervention at a key young age.

Further research is required to ensure all these infants are correctly managed. The US-based multicentre, prospective Maternal and Fetal Outcomes in the Era of Modulators (MAYFLOWERS) study (10) is investigating the association between maternal CF-health parameters and CFTRm-use but does not include a longitudinal assessment of the ‘obligate CFTR-heterozygote’ offspring. This study aims to start filling this gap in knowledge by providing high quality data, which will support further investigation and ultimately the production of guidelines on follow up practices for these infants.

